### Data collection

Each township health center is responsible for the recruitment and training of data collectors. The data collector will help participants complete a questionnaire and collect physical examination information at the 1, 3, 6, 9, and 12 months (Fig. 3). This study uses the 2020 National Residents’ Health Literacy Monitoring Questionnaire, which includes three basic aspects and six categories of questions about health literacy [33]. Points are scored according to questions related to the questionnaire, meaning 1 point for correct answers to single-choice questions and 0 point for incorrect answers, 2 points for correct answers to multiple-choice questions and 0 points for incorrect answers (less choice, more choices, and wrong choice are all judged as wrong answers). The total score of the questionnaire is 66 points.

**Fig. 3 Fig3:**
[figure not shown]
SPIRT Figure

Data collectors will also collect information on smoking and alcohol consumption, and measure participants’ height, weight, blood pressure, and blood sugar. The sponsor of family branch will inform the participants of the time and place of measurement, and the need to fast for one night. All participants will be informed of the study information orally and in writing, prior to the questionnaire and physical examination, and their data will be collected only after providing written informed consent.

Data collection will follow standard data management protocols. The research will provide suitable survey sites, and assign special personnel to be responsible for on-site supervision, double data entry, data coding, data verification, and data preservation. Only members of the research team have access to the data, and identifiable data will not be collected and will be replaced by serial numbers to reduce the risk of privacy disclosure, so there will be no risk to residents’ privacy.

### Sample size and sampling method

This study is an open cohort design. Since the withdrawal of the original cohort participants and the addition of new participants during the progress of the longitudinal study are allowed, the number of trial measurements may be different for each participant. Hence, after discussion with local experts, this study intends to set the participation retention rate to 0.6.

Use the formula for calculating the sample size of an open cohort SW-CRT proposed by Kasza et al. in 2020 [36], assuming that there are 50 subjects in each cluster-period, the intra-cluster correlation coefficient is 0.4, the cluster autocorrelation coefficient is 0.9, the individual autocorrelation coefficient is 0.7, the total variance is 19, and decays in between-period correlations and participant-level correlations are allowed. On the significance level α = 0.05, the 1 difference of outcome effect after intervention would be found. At the same time, in order to ensure 80% power, the minimum number of clusters required is 7.699, rounded up to 8, making the total test subjects are 400 cases. In order to take non-response into account, we expanded the sample size by 30%, and obtained 572 subjects and 11.44 clusters. After rounding the number of clusters, finally, 600 subjects from 12 family branches will participate in the study. Using R 4.0.5 to generate random numbers and assign a unique number to each recruited family branch in Meigu County and Yanyuan County. Simple random sampling will be used to select 6 family branches from Meigu County and Yanyuan County respectively, and completely randomized into 4 groups independently. In the next stage, a random sample of 50 eligible individuals will be stratified by gender and age within each family branch. The generation of random allocation sequence and allocation are completed by a third-party independent statistician.

The Meigu County and Yanyuan County carry out various health education activities for residents’ health literacy annually. This study will enrich the health literacy improvement plan under local routine management work. Due to the low education level and relatively occluded information in the study sites, it is difficult for subjects to perceive transition from the non-intervention state to the intervention state, ensuring implementation of blinding for the subjects to some extent.

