#### Open cohort stepped wedge cluster randomized trial design

For this study, *N* family branches in the Meigu and Yanyuan County will be included. Each family branch is regarded as a cluster, and *A* clusters constitute a group. It is assumed that there are *N* / *A* groups in the study, the first and third groups are in Meigu County and the second and fourth groups are in Yanyuan County. The experimental study period of the whole project is 1 year, from May 2022 to May 2023. All groups are in non-intervention during the first 3 months (Phase1) of the project. In the second 3 months (Phase2), groups 1 and 2 will start to receive intervention. Then 3 months later (Phase3), groups 3 and 4 will begin to receive intervention. According to the research proposal, all groups will continue to increase 3-month follow-up (Phase4), after all of them having received intervention in a random order, ensuring that study outcomes can be observed when time lag effect of intervention exists (Fig. 1).

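### The printed sample-size inputs require about 31 family branches in total for 80% power, not 7.699; the planned 12 branches give about 42% power for a 1-point difference

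*Protocol article*

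**What the plan says.** All of the inputs are in the protocol article, under Sample size and sampling method. The calculation is run "assuming that there are 50 subjects in each cluster-period, the intra-cluster correlation coefficient is 0.4, the cluster autocorrelation coefficient is 0.9". It puts 0.7 on the correlation between repeated measurements of one resident and 19 on the variance of the outcome, and it lets the correlations at both levels weaken with time. The retention rate is set at 0.6. The target is given as "On the significance level α = 0.05, the 1 difference of outcome effect after intervention would be found", and the power as 80%.

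The result is that "the minimum number of clusters required is 7.699, rounded up to 8, making the total test subjects are 400 cases". The total of 400 (8 × 50) shows that 7.699 is taken as the number of branches in the whole trial. After an allowance of 30% for non-response, "finally, 600 subjects from 12 family branches will participate in the study". These are allocated to four groups, so three branches per group.

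The design section fixes the schedule. All groups are untreated in Phase 1 and groups 1 and 2 start in Phase 2. "Then 3 months later (Phase3), groups 3 and 4 will begin to receive intervention". Phase 4 is further follow-up with every group treated. There are therefore four groups but only two distinct crossover dates.

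**The concern.** With an intra-cluster correlation of 0.4, most of the uncertainty in a branch mean comes from differences between branches, and adding residents within a branch reduces it little. The standard deviation of the outcome is √19 ≈ 4.4 points, so a difference of 1 is small. The two crossover dates also differ in only one phase: Phase 2 is the only time when treated and untreated branches are observed together. Eight branches looked far too few for 80% power under these conditions.

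This one figure sets the size of the trial. If it is wrong, the trial is described as adequately powered when it is more likely than not to miss the effect it was sized for. A non-significant result would then say much less than readers of the protocol would assume.

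**Working it through.** **Inputs (Sample size and sampling method, unless noted).** m = 50 per cluster-period; ICC 0.4; cluster autocorrelation 0.9; individual autocorrelation 0.7; both decaying with the distance between periods; retention 0.6; total variance 19; difference 1; α = 0.05; power 80%. The schedule is from the design section. Fixed period effects and generalised least squares are from the mixed-effects model section. One assumption is mine: α is two-sided, since the article does not say.

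**Covariance of the branch-period means.** The between-branch part is 19 × 0.4 = 7.6 and the individual part is 19 × 0.6 / 50 = 0.228.
- Same period: 7.6 + 0.228 = 7.828
- One period apart: 7.6 × 0.9 + 0.228 × 0.7 × 0.6 = 6.9358
- Two periods apart: 7.6 × 0.81 + 0.228 × 0.49 × 0.6 = 6.2230

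**Variance of the effect, Phases 1 to 3 (sequences 011 and 001, half the branches each).** The sequences differ only in Phase 2, so N × Var(δ) = 4 × the variance of the Phase 2 mean given the Phase 1 and Phase 3 means:

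7.828 − 2 × 6.9358² / (7.828 + 6.2230) = 0.9809, so N × Var(δ) = 3.923.

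**Branches required.** (1.960 + 0.842)² = 7.849, and 7.849 × 3.923 / 1² = **30.79 branches in total**.

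**Reproducing the printed figure.** 30.794 / 4 groups = 7.6986, which rounds to the printed 7.699. With all four phases (0111 and 0011) the total is 30.76 and the per-group figure is 7.691, so the three-decimal match needs the three-period version. Requirement scales as variance / difference², so dividing by 4 is algebraically the same as using a difference of 2, or a variance of 19 / 4 = 4.75. Either would give 7.699 as a total.

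**Power of the planned trial (four phases, N × Var = 3.919).**

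| Branches | Basis | SE | Power for 1 point |
|---|---|---|---|
| 8 | normal, 50 responding | 0.700 | 30% |
| 12 | normal, 50 responding | 0.571 | 42% |
| 12 | normal, 35 responding | 0.594 | 39% |
| 12 | t on 10 df, 50 responding | 0.571 | 35% |
| 12 | t on 10 df, 35 responding | 0.594 | 33% |

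For the second row: Φ(1/0.5715 − 1.960) = Φ(−0.210) = 0.417. The t rows use the non-central t distribution. The detectable difference with 12 branches is 2.802 × 0.5715 = 1.60 points (1.66 with 35 responding).

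**Other readings of the design, still at ICC 0.4 and cluster autocorrelation 0.9.** Totals required:
- Five measurement rounds: 30.7
- Retention falling geometrically: 30.4
- Closed cohort: 27.5
- Repeated cross-sections: 35.5
- Unlimited residents per branch: 25.0
- One-sided α: about 24

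None comes near 8 or 12.

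**The inflation step.** 400 / 0.7 = 571.4, taken as 572, and 572 / 50 = 11.44. This agrees with the article. The problem is the starting number of 8.

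**The case against.** The strongest objection is that the cause is not established. A reader might infer that 7.699 is certainly a per-group count. The article never says so. The exact match needs three periods although the article describes four phases, and a target difference of 2 would explain the figure equally well. In that case 8 branches would be right and the printed 1 would be the error. This objection stands: the per-group explanation is probable but not proven. It does not rescue the paragraph as written, because either way the printed inputs and the printed power disagree.

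A reader might also infer that 12 branches could reach 80% only with a much smaller ICC, near 0.05. That is not so. With the ICC kept at 0.4, a cluster autocorrelation of about 0.974 instead of 0.9 would also make 12 enough. The result is sensitive to that input, which is a further reason for the authors to recheck all of them.

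Nor should the corrected total simply be divided by 0.7 for non-response, as the article does with its own. At this ICC, 35 responders per branch raises the requirement only from about 31 to about 33 branches.

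Finally, the Discussion describes the trial as exploratory. That may justify a small trial, but it does not justify stating 80% power for it. Nor is this a detail left to an analysis plan: the article prints a complete calculation.

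**Conclusion.** The stated 80% power is wrong under the article's own inputs. About 31 branches in total are needed for a difference of 1, against 8 called sufficient and 12 planned. Twelve branches give about 42% power at best. Allowing for non-response alone gives 39%, a small-sample reference alone 35%, and both together 33%. The detectable difference is at least about 1.6 points.

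This rests on two-sided α, the two crossover dates in the design section, retention of 0.6 between any two periods, and the printed correlations and variance. The shortfall does not depend on why 7.699 was printed. Which quantity was misread or misprinted cannot be decided from the document.

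**What to change.** The authors should rerun the calculation, state the number of periods, the crossover sequences and the sidedness used, and say whether 7.699 is a total or a per-group count.

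- **If the printed inputs stand and 12 branches is the feasible number:** remove the 80% power claim. State power of about 35–42% for a 1-point difference (33% with both allowances together) and a detectable difference of at least about 1.6 points.
- **If an input was misprinted, for example the difference:** correct it, justify the value, and restate the power for it. For illustration, a difference of 2 with 12 branches would give Φ(2/0.5715 − 1.960) = Φ(1.54), about 94% by normal approximation.

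The cost is one rerun and a text correction, together with a less favourable stated power if the inputs stand. Neither route requires more branches or a change to the schedule.

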#### Outcome

The primary outcome of the project is the health literacy level of residents in the *Health Liangshan Yi Autonomous Prefecture Performance Evaluation Index*, which is defined by the 2020 *Residents Health Literacy Monitoring Questionnaire* [33].

The secondary outcomes are prevalence of hypertension, prevalence of diabetes, BMI, smoking intensity index [34], and alcohol consumption [35]. The project will measure the outcome indicators at 1, 3, 6, 9, and 12 months.

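### The 400 and 600 given as trial totals are headcounts per round; keeping 50 per branch per period at 0.6 retention needs more than 600 distinct residents

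*Protocol article*

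**What the plan says.** All the sample size inputs are in the protocol article under Sample size and sampling method.

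- The cohort is open: "the withdrawal of the original cohort participants and the addition of new participants during the progress of the longitudinal study are allowed".
- On turnover, "this study intends to set the participation retention rate to 0.6". No interval is attached to this rate.
- The power formula is applied "assuming that there are 50 subjects in each cluster-period".
- The result is that "in order to ensure 80% power, the minimum number of clusters required is 7.699, rounded up to 8". The section multiplies 8 by 50 and describes the resulting 400 as the total number of subjects.
- After a 30% allowance for non-response it reaches 572 subjects and 11.44 clusters, rounds up to 12 branches, and ends with "finally, 600 subjects from 12 family branches will participate in the study".
- One stratified random sample of 50 eligible residents per branch is described. No later draw to replace leavers is mentioned.

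The design section sets out four three-month phases. The Outcome section gives five measurement rounds: "The project will measure the outcome indicators at 1, 3, 6, 9, and 12 months".

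**The concern.** In an open cohort, the number measured at each round and the number of different people who ever take part are two separate quantities. The power formula uses the first. The article computes the first but labels it as the second.

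The statements do not fit together. If 600 is the number of people in the trial, a branch cannot still have 50 at later periods once 40% have left. If 50 per period is kept, more than 600 people take part.

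What is at stake is mainly practical. The numbers of residents to consent, interview and examine follow the distinct total. So does the number of eligible residents a branch must have before it can supply the design. A field team that takes 600 as the target and follows the single sampling step described would not deliver the cluster-period size assumed in the power calculation.

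**Working it through.** **Inputs from the article.** 50 per cluster-period, retention 0.6, 8 then 12 branches, 30% non-response, ICC 0.4, cluster autocorrelation 0.9, individual autocorrelation 0.7, total variance 19, detectable difference 1, alpha 0.05 (taken as two-sided). Four phases; five rounds.

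**Step 1: reproduce the stated figure.**
- 7.699 rounds up to 8; 8 x 50 = 400.
- 400 / (1 - 0.30) = 571.4, rounded up to 572.
- 572 / 50 = 11.44, rounded up to 12.
- 12 x 50 = 600.

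Every link reproduces. None contains a factor for the number of periods or for turnover, so 400 and 600 are both headcounts at one round.

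**Step 2: distinct residents if 50 per branch is kept.** With 0.6 retained, 50 x (1 - 0.6) = 20 places per branch must be refilled at each interval to which the rate applies. If leavers do not return, a branch needs 50 + 20 x (number of such intervals).

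| What 0.6 refers to | Per branch | 12 branches | 600 as a share |
|---|---|---|---|
| Whole year (one loss) | 50 + 20 = 70 | 840 | 71% |
| Between four phases (three losses) | 50 + 3 x 20 = 110 | 1,320 | 45% |
| Between five rounds (four losses) | 50 + 4 x 20 = 130 | 1,560 | 38% |

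All three exceed 600.

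**Step 3: what happens if leavers are not replaced.** With 0.6 per phase, branch sizes are 50, 30, 18 and 10.8. The sum is 108.8 per branch, so 12 x 108.8 = 1,306 person-measurements over the four phases. The assumed design has 12 x 50 x 4 = 2,400.

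**Step 4: effect on power.** I took the generalized least squares variance of the intervention effect from cluster-period means, with 12 branches, four periods, two crossover times and decay at both levels. For full periods of m = 50, the covariance of two means d periods apart is 19 x [0.4 x 0.9^d + 0.6 x 0.7^d x R(d)/50], where the factor 0.6 before 0.7^d is 1 - ICC and R(d) = 0.6^d is the share of residents common to both periods. Power is Phi(1/SE - 1.96).
- With replacement: SE 0.568, power 42%.
- Without replacement (50, 30, 18, 11): SE 0.583, power 40%.

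At an ICC of 0.4 the between-branch variation dominates, so losing residents within branches costs little. At an ICC of 0.1, which is my assumption and not in the article, the SEs are 0.388 and 0.417 and the powers 73% and 67%.

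The same calculation needs about 30 to 31 clusters for 80% power. That concerns the 7.699 and is a different point.

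**The case against.** The best defence is that nothing is miscalculated. The section opens by allowing newcomers and then draws an initial sample of 50 per branch, so 600 could be a starting sample with joiners on top, and the count of joiners could be left to the full protocol. The arithmetic does hold at every link. The starting-sample reading does not fit the words, however: 400 is called the total, and 600 is the number who will take part in the study. A condensed article may omit the replacement procedure, but a total that it does state should agree with its own inputs. The 30% allowance does not repair this either. It is spent on more branches and leaves 50 per branch unchanged.

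Other parts of the defence stand. A reader might infer that 600 is about half of the true enrolment, or that a branch with fewer than about 110 eligible residents cannot supply the design. The article supports neither. Both need 0.6 to apply between phases and leavers never to return. The Background links turnover to migrant work, so returns are plausible. If leavers re-enter from a fixed pool of 50/0.6 = 83 per branch, the total is about 1,000. Branch sizes are not given, so no shortage is shown.

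A reader might also call 600 the number needed at each round. On the article's own arithmetic that need is 400, and 600 adds non-response and rounding.

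Finally, a reader might infer a serious loss of power. At the stated ICC it is about two percentage points.

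**Conclusion.** The point holds as a fault in the enrolment figure and its feasibility. The article presents per-round headcounts of 400 and 600 as trial totals, and its own inputs imply more than 600 distinct residents. The size is about 840, 1,320 or 1,560, depending on whether 0.6 is a whole-year, per-phase or per-round rate. These figures assume that 50 per branch is kept and that leavers do not return. The direction does not depend on that choice, but the multiplier does, so no single factor should be quoted until the interval is defined.

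This is not the reason the design falls short of 80% power. With 12 branches at an ICC of 0.4, power is about 42% with replacement and 40% without. The gap to 80% comes from the cluster count and needs its own correction. If the number of branches changes, the totals here scale with it.

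**What to change.** 1. State the size as 50 residents per branch per round, which is 600 per round with 12 branches, and say that this includes the non-response allowance and rounding. Relabel the 400 for 8 branches in the same way.
2. Define the interval to which 0.6 applies and say whether leavers may return.
3. Give the expected number of distinct residents that follows: 840, 1,320 or 1,560 without re-entry.
4. Before sampling, check each branch's list of eligible residents against the matching figure: 70, 110 or 130.
5. If leavers will not be replaced, say so and redo the calculation with falling cluster-period sizes (50, 30, 18, 11 if 0.6 is per phase).

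The cost is a few sentences of protocol text and a count of eligible residents per branch. The published enrolment figure becomes larger, and fieldwork has to be planned for it. The Study status section says recruitment was still being prepared at publication, so the change could be made before branches are sampled.

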##### Step 2. Promotion within family branch

The sponsor of each famliy branch will use the health literacy knowledge brochures to educate other members in famliy branches on health literacy according to the operating manual. We encourage all members of famliy branches to participate in the project, identify problems, propose and implement solutions, conduct self-evaluation and measure improvement. Besides, we require each famliy branch to hold at least one collective sharing meeting monthly.

In terms of nutrition education, we will design and produce nutrition education playing cards in the form of popular 4 or 6 sentences, which are repeatedly revised and proven by a number of nutrition experts. The contents mainly include Chinese dietary guidelines and balanced diet pagoda, the function of nutrients and their main food sources, the nutritional value of various foods, dietary guidance for specific populations and patients with common NCDs, aerobic exercise, weight evaluation and its impact on health, food safety problems, the harm of excessive smoking and drinking, etc. The nutrition education methods will include the following: (1) Distribute nutrition education cards, introducing their main contents and carrying out a quiz on the contents of the cards. Train the sponsors to explain the cards to other family members through their publicity. (2) Distribute nutrition health knowledge publicity materials, and ask the use of the cards to supervise. (3) Set up nutrition knowledge bulletin boards and post nutrition health knowledge bulletin materials. (4) Start nutrition knowledge courses and lectures. (5) Set up personalized online or offline nutrition counseling and guidance stations which are mainly based on the actual dietary situation of the residents, and provide relevant dietary nutrition guidance after analysis.

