##### Step 3 competition between family branches

Take advantage of traditional Yi festivals to conduct health literacy knowledge competitions on a regular basis by family branches. We will distribute the prizes according to the competition rankings, and issue the honorary certificates to the family branches with outstanding scores. Use the concept of family honor of Yi nationality to stimulate the internal motivation of residents to improve health literacy, exam and test the actual mastery of health literacy knowledge through competitions and other means.

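### The partial blinding of participants claimed in the protocol does not fit an intervention of monthly meetings, quizzes and ranked prizes; participants should be treated as aware of it

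*Protocol article*

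**What the plan says.** The last paragraph of Sample size and sampling method claims partial blinding of participants. Citing residents' limited schooling and information, it says that "it is difficult for subjects to perceive transition from the non-intervention state to the intervention state, ensuring implementation of blinding for the subjects", and the conclusion carries a qualifier: "ensuring implementation of blinding for the subjects to some extent". The context offered is that both counties already run health education every year and that the study adds to this routine work.

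Other sections describe what changes for a family branch at crossover and what participants are told:

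- Step 1, Core group building: a sponsor is recruited for the branch, examined in writing and by interview, and trained.
- Step 2, Promotion within family branch: all members are urged to join in and to evaluate themselves. Card quizzes, bulletin boards, lectures and counselling stations are introduced, and "we require each famliy branch to hold at least one collective sharing meeting monthly".
- Step 3, Competition between family branches: contests are held at Yi festivals. "We will distribute the prizes according to the competition rankings, and issue the honorary certificates to the family branches with outstanding scores".
- Data collection: "All participants will be informed of the study information orally and in writing, prior to the questionnaire and physical examination", with written consent before any data are taken.

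On measurement, Data collection has collectors assist participants with the questionnaire that yields the primary score. They also gather smoking and alcohol information and measure height, weight, blood pressure and blood sugar.

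**The concern.** A blinding statement tells readers how far to discount bias from participants' knowledge of their treatment. Here the stated reason concerns residents' education and access to information, whereas the activities take place in front of them and ask for their involvement. Step 3 even relies on family honour as the motive, which works only if residents know about the contest.

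If the sentence stands, a reader may take differences in reported behaviour, or in a score obtained with a collector's help, as protected by blinding when they are not. Smoking and alcohol are the clearest case, because Step 2 teaches the harms of both before the treated residents are asked about them.

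**Working it through.** The blinding claim rests on no figure, so there is none to reproduce. The check sets the sections side by side, then traces how a bias would enter the model.

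**1. Can the switch be perceived?**

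| Feature | Section | Visible to residents? |
|---|---|---|
| Examined and trained branch sponsor who teaches members | Steps 1 and 2 | Yes, a new role within the branch |
| Sharing meeting at least monthly | Step 2 | Yes, required of every branch |
| Quizzes, bulletin boards, lectures, counselling stations | Step 2 | Yes |
| Festival contests with rankings, prizes, certificates | Step 3 | Yes, public by design |
| Oral and written study information | Data collection | Yes, all participants |

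The control condition is the routine Contracted Family Doctor Services, which the Background describes as including pushed health information. None of the first four features is described as part of it. Limited schooling may keep a resident from knowing the trial design, but it does not hide a new monthly meeting or a prize-giving.

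**2. Where would a bias go?** By the design section, Phase 1 has no treated group, Phase 2 has groups 1 and 2 treated and groups 3 and 4 untreated, and from Phase 3 all are treated. Phase 2 is therefore the only stage in which treated and untreated groups are seen at the same time. The model mean is

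E[Y_ij] = μ + β_j + δ·X_ij.

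If a bias b starts with treatment and persists, then

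E[Y_ij] = μ + β_j + (δ + b)·X_ij.

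The coefficient on X_ij now estimates δ + b. The stage effect β_j is common to all groups within a stage and cannot absorb b. Help or misreporting that is equal in control and intervention periods does not enter this coefficient; only the differential part does.

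**3. Which outcomes are exposed?**

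- Smoking and alcohol: apparently self-reported (the article says only that information is collected), so most exposed.
- Primary score: items marked right or wrong, so not self-report. It is exposed through motivation and the collector's help.
- BMI, blood pressure and blood sugar: measured, so less exposed.

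**4. How large might it be?** The documents give no bias figure. The following is illustration only. It assumes that the target difference of 1 is one point of the 66-point score, a unit the article does not state.

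- Inputs: total variance 19 (Sample size); 1 point per single-choice item and 2 per multiple-choice item (Data collection).
- 1/66 = 1.5% of the scale; √19 = 4.36; 1/4.36 = 0.23 SD.
- The target equals one single-choice item, or half of one multiple-choice item. Differential help with one single-choice item for one treated participant in four would give b = 0.25 × 1 = 0.25 points.

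Taking the stated 80% power at face value, with a two-sided 5% test assumed, the implied SE is 1/(1.960 + 0.842) = 0.357. With no true effect, P(|Z + b/SE| > 1.96) is:

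| Assumed b (points) | Chance of a significant result |
|---|---|
| 0.10 | 6% |
| 0.25 | 11% |
| 0.50 | 29% |
| 0.75 | 56% |
| 1.00 | 80% |

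Whether that power is right is a separate question. A larger SE would lower these percentages but leave b in the estimate unchanged.

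**The case against.** The best defence is that the protocol claims little. The sentence is qualified, both counties already run health education, and the control services also send out health information, so some residents may see only more of the same. The plan itself expects never-takers, and nothing says that the consent information discloses the crossover date. This stands to the extent that one cannot say every treated resident will know. It does not rescue the stated reason: most residents will be able to notice the new meetings, contests and prizes.

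The article also contains safeguards. Quality control lists standard procedures, survey instructions, training manuals, unified training and recorded interviews, and Data collection adds on-site supervision. Helping people of low literacy with a form does not mean giving answers. This is fair, and it is why the remedy builds on those measures. No planned analysis depends on blinding, so the harm lies in interpretation.

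A reader might infer several stronger things that the documents do not support:

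- That data collectors are unmasked. The article is silent, and a condensed article may leave this to the full protocol. Recruitment of sponsors by township hospitals and of collectors by township health centres does not show that collectors know a branch's state.
- That branch honour depends on the study questionnaire. Prizes follow the festival contests, and no section links them to questionnaire scores.
- That the outcomes in general are self-reported. The primary outcome is a right/wrong test, and several secondary outcomes rest on measurement.
- That a bias as large as the target has been shown. It has not.

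**Conclusion.** The protocol states a property that the design does not have. Participants cannot be regarded as blinded, even in part, on the ground given. This conclusion rests on comparing sections of the article and needs no assumption about the size of a bias or about the masking of collectors.

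The consequence is conditional: if awareness or assistance changes answers differentially, the change is counted as intervention effect. Its size is unknown. The reading of the target as one single-choice item (0.23 SD) shows only that a small differential would matter if the target is in score points. The trial remains viable, and randomisation, sample size and model are unaffected. What needs correction is the statement, the undefined help, and the weight given to reported behaviour.

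**What to change.** - In Sample size and sampling method, delete the sentence on blinding and state that the trial is open-label for participants.
- In Data collection, define the collector's help as reading items and options aloud without explanation or prompting, done identically in control and intervention periods.
- Use the interview recordings already planned under Quality control to check a sample of Phase 2 interviews, from treated and untreated branches alike, for prompting.
- Report smoking and alcohol as reported outcomes open to reporting bias, and rest claims of health change mainly on the measured outcomes.

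The cost is a change of wording, a little extra training and some time to review recordings. Moving collectors between townships is not proposed. The Study site section describes difficult mountain travel, investigators must speak the dialect, and visible materials in a branch would probably reveal its state anyway.
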